## Brief description of the collected data and statistical power

The final dataset was created in June 2011 and included data on 7,806 melanoma cases, 3,151 NMSC cases (2,211 BCC, 788 SCC and 152 with both), and 14,875 controls.

Distribution of data according to study country in which the study was performed is presented in Table 2. The majority of data came from Europe, especially from southern European populations. There was no significant difference in participation rate according to study area (Fisher exact test p-value: 0.25).

**Table 2 T2:** Summary of data included in the M-SKIP project by geographical location

**Study area**	**Invited investigators**	**Participant investigators (studies)**	**Melanoma cases**	**NMSC cases**	**Controls**
Africa	1	0 (0)	0	0	0
Asia	3	2 (2)	0	0	345
Australia	4	2 (3)	744	298	290
Northern Europe^a^	8	6 (6)	858	1629	8095
Central Europe^b^	6	3 (4)	977	639	2398
Southern Europe^c^	9	8 (12)	2,747	0	2263
North America	13	11 (12)	2,480	585	1484
**TOTAL**	**43**^**d**^	**31**^**d**^**(39)**	**7808**	**3151**	**14875**

*NMSC* = non melanoma skin cancer.

^a^ includes Denmark, Norway, Sweden, The Netherlands, UK.

^b^ includes France, Germany, Poland.

^c^ includes Greece, Italy, Spain.

^d^ one investigator collected data for two different areas (North America and Asia).

The main characteristics of the studies included in the M-SKIP database are described in Table 3. The majority are case–control studies (54%) with population or healthy controls and case–control matching. Phenotypic characteristics were frequently assessed by self-administered questionnaire (41%) or examination by a dermatologist or research nurse (36%). The majority of studies sequenced the entire coding region of the *MC1R* (67%) and used blood as DNA source (62%).

**Table 3 T3:** Main characteristics of the included studies

	**Studies (%) N = 39**	**Melanoma cases (%) n = 7806**	**NMSC cases (%) n = 3151**	**Controls (%) n = 14875**
**Study design**				
Case–control	21 (54%)	5092 (65%)	2052 (65%)	6852 (46%)
Case only	11 (28%)	2646 (34%)	0	0
Control only	6 (15%)	0	0	1464 (10%)
Cohort	1 (3%)	68 (1%)	1099 (35%)	6559 (44%)
**Source of controls**				
Hospital	6 (21%)	509 (10%)	1169 (37%)	1847 (12%)
Population or healthy^a^	21 (75%)	4651 (90%)	1982 (63%)	12872 (87%)
Mixed	1 (4%)	0	0	156 (1%)
**Case–control matching**^**b**^				
No	10 (45%)	3151 (61%)	1739 (55%)	9578 (71%)
Yes	12 (55%)	2009 (39%)	1412 (45%)	3833 (29%)
**Phenotype assessment**				
Self-administered questionnaire	16 (41%)	2768 (35%)	672 (21%)	1875 (13%)
Examination by an expert	14 (36%)	3970 (51%)	1380 (44%)	4392 (30%)
Instrumental measure	2 (5%)	0	0	222 (1%)
Mixed	5 (13%)	297 (4%)	1099 (35%)	7247 (49%)
No measure	2 (5%)	771 (10%)	0	1139 (8%)
**Genotype assessment**				
Sequencing analysis	26 (67%)	5942 (76%)	1059 (34%)	4813 (32%)
Others^c^	13 (33%)	1864 (24%)	2092 (66%)	10062 (68%)
**DNA source**				
Blood	24 (62%)	4645 (60%)	2743 (87%)	13304 (89%)
Buccal cells	14 (36%)	3161 (40%)	408 (13%)	1326 (9%)
Tissue	1 (3%)	0	0	245 (2%)

*NMSC* = non melanoma skin cancer.

^a^ healthy subjects are blood donors, friends or relatives of cases.

^b^ individual or frequency.

^c^ includes RFLP, SNaPshot, allele discrimination assay.

We calculated that the minimum required sample size to find a statistically significant association between a *MC1R* variant and melanoma assuming a similar association to that observed in our previous meta-analysis [14] (Odds Ratio (OR) = 1.5) is around 7,500 cases and 7,500 controls for rare variants (1-2% allele frequency in controls), and 1,400 cases and 1,400 controls for common variants (8-10% allele frequency in controls), with 90% statistical power. Sample size for gene-environment interaction analysis was also calculated with the program POWER, version 3.0 [96]. Considering the study of a simple two-way interaction between an environmental factor and a rare *MC1R* variant, around 5,000 cases and 5,000 controls would be needed to observe a multiplicative interaction effect of 2.0, arising to 16,000 cases and 16,000 controls to observe a smaller multiplicative effect of 1.5, both with 90% statistical power. For common *MC1R* variants, the same gene-environment interaction effects of 2.0 and 1.5 could be observed with around 1,200 cases and 1,200 controls, and with around 3,500 cases and 3,500 controls, respectively. Our sample size therefore is appropriate for the purpose of the analysis, and large enough to allow stratified and interaction analyses, especially to find even small interaction effects with the most frequent variants, and larger interaction effects for less common variants.

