## The M-SKIP project: rationale and aims

Melanocortin-1-receptor (*MC1R*, MIM#155555) is one of the major genes that determine skin pigmentation and it has been reported to be associated with risk of melanoma [14], possibly through the determination of the tanning response of skin to UV radiation [15-17]. However the relationship between some *MC1R* variants and melanoma also in darkly-pigmented European populations suggests that *MC1R* signaling may have an additional role in skin carcinogenesis beyond the UV-filtering differences between dark and fair skin [18]. In previous meta-analyses [14,19,20] authors found evidence of a significant association between melanoma, red hair and fair skin and the five *MC1R* variants R151C, R160W, D294H, D84E and R142H, and suggested a possible role in melanoma development, via non-pigmentary pathways, for I155T and R163Q variants. However, the specific contribution of each *MC1R* variant to melanoma development via pigmentary and non-pigmentary pathways could not be evaluated in meta-analyses due to the lack of individually joint information on *MC1R* variants and phenotypic characteristics.

The aim of the M-SKIP project is therefore to perform a pooled-analysis of individual data on sporadic skin cancer cases and controls with information on *MC1R* variants, in order to: 1) assess the association of *MC1R* variants with melanoma, basal cell carcinoma (BCC) and squamous cell carcinoma (SCC); 2) assess the association between *MC1R* variants and phenotypic characteristics, including hair and eye color, skin color, skin type, common and atypical nevi, freckles, and solar lentigines; and 3) perform stratified analyses on *MC1R* variants and skin cancer by phenotypic characteristics, and evaluate *MC1R*-phenotype interaction in skin cancer risk.

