### Two-stage analysis with random effects models

The two-stage analysis method [100] will allow us to overcome the problem of the availability of different study covariates. The pooled-estimates of the association of *MC1R* variants with each skin cancer type and each phenotypic characteristic will be calculated as follows.

First, study-specific ORs will be calculated by applying logistic regression to the data from each study to estimate the odds of skin cancer conditional on the presence of a *MC1R* variant (*X*), controlling for confounders *Z*_*k*_. For study *k* (*k = 1,…,K*), assuming just one confounder, the model is written as:

(4)$$\text{logit}(\pi_{\mathrm{ik}}/X)=\alpha_{k}+\beta_{k}X_{\mathrm{ik}}+\gamma_{k}Z_{\mathrm{ik}}$$

where *π*_*ik*_ is the conditional probability of skin cancer for subject *i* (*i = 1,…,n*_*k*_) of study *k*. Although *MC1R* variants were uniformly defined across studies, the confounders *Z*_*k*_ may be specific to a particular study. Analyses with original covariates and with recoded data will be performed and compared. The exposure log-odds ratio for study *k* is denoted *β*_*k*_, the confounding log-odds ratio is denoted *γ*_*k*_, and the *α*_*k*_ are the study-specific intercepts. The *β*_*k*_ are assumed to vary across studies according to the second-stage model:

(5)$$\beta_{k}=\beta +b_{k}+e_{k}$$

where *β* is the pooled-exposure log-odds ratio, *b*_*k*_ are random effects with *b*_k_ ~ N(0, *σ*^*2*^_*b*_), where *σ*^*2*^_*b*_ represents the variability of the study-specific exposure effects *β*_*k*_ about the population mean *β,* and *e*_*k*_ are independent errors with *e*_k_ ~ N(0, *σ*^*2*^_*k*_), where *σ*^*2*^_*k*_ describes the within-study variation of the *β*_*k*_. In the first stage ${\hat{\beta }}_{k}$and its variance ${\hat{\sigma }}_{k}^{2}$ are estimated from equation 4, separately for each study.

The two-stage estimator of the pooled exposure effect *β* is a weighted average of the ${\hat{\beta }}_{k}$, weighted by the inverse marginal variances of the ${\hat{\beta }}_{k}$, denoted $w_{k}={\left({\hat{\sigma }}_{k}^{2}+\sigma_{b}{}^{2}\right)}^{-1}$. Thus:

(6)$$\hat{\beta }=(\sum_{k}w_{k}{\hat{\beta }}_{k})/\sum_{k}w_{k}$$

(7)$$\mathrm{var}(\hat{\beta })={\left(\sum_{k}w_{k}\right)}^{-1}$$

Two methods [100] are frequently used to estimate the random effects variance *σ*^*2*^_*b*_ in equations 6 and 7. These methods are pseudo-maximum likelihood and moment estimation.

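### The sample is declared adequate for the whole analysis from a main-effect calculation for melanoma only; at the same odds ratio SCC falls short of 90% power for rare variants on every reading, and BCC on some

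*Protocol article*

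**What the plan says.** Aim 1, in the section on rationale and aims, is to "assess the association of *MC1R* variants with melanoma, basal cell carcinoma (BCC) and squamous cell carcinoma (SCC"). The section on two-stage analysis plans separate estimates: the pooled associations of "variants with each skin cancer type and each phenotypic characteristic will be calculated as follows". The section on joint association repeats the split by cancer type for the stratified analyses and logic regression.

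The sample-size paragraph closes the section *Brief description of the collected data and statistical power*. Its main-effect calculation concerns a "variant and melanoma assuming a similar association to that observed in our previous meta-analysis" ("Odds Ratio (OR) = 1.5"). The minimum size at 90% power "is around 7,500 cases and 7,500 controls for rare variants (1-2% allele frequency in controls"), and 1,400 of each for common variants at 8–10%. Interaction requirements follow, with no cancer type named. For rare variants they are 5,000 + 5,000 (effect 2.0) and 16,000 + 16,000 (effect 1.5). For common variants they are 1,200 + 1,200 (effect 2.0) and 3,500 + 3,500 (effect 1.5).

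The paragraph then concludes: "Our sample size therefore is appropriate for the purpose of the analysis, and large enough to allow stratified and interaction analyses". The rest of that sentence qualifies the interaction claim by variant frequency. It does not qualify anything by cancer type. The same section reports 7,806 melanoma cases and "3,151 NMSC cases (2,211 BCC, 788 SCC and 152 with both), and 14,875 controls".

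**The concern.** The conclusion covers the purpose of the analysis as a whole, but the main-effect calculation behind it covers one of the three cancers in aim 1. The melanoma count exceeds the stated 7,500. The BCC and SCC counts do not come near it, and no separate requirement is given for them.

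If the sentence stands, readers of the eventual results will take rare-variant estimates for SCC, and possibly BCC, to come from a sample that was planned to be large enough. At the assumed OR, a non-significant rare-variant result for SCC would be a likely outcome even if the association were real. Melanoma has about eight times as many cases as SCC (7,806 / 940 = 8.3), so a contrast in significance between the two could arise from case numbers alone.

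**Working it through.** **Inputs.** BCC cases: at most 2,211 + 152 = 2,363. SCC cases: at most 788 + 152 = 940. Those with both tumours are counted in each outcome, which is the generous choice. Controls: Table 2 shows no NMSC cases in Africa, Asia or Southern Europe, so controls from areas with any NMSC case number at most 290 + 8,095 + 2,398 + 1,484 = 12,267. Assumptions: two-sided 5% (the article states no alpha), OR 1.5 carried over from melanoma, complete data, one stratum, no between-study variance.

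**Step 1: reproduce the stated requirement.** The two-proportion formula with continuity correction, 90% power, equal groups and p1 = 1.5·p0 / (1 + 0.5·p0), gives:
- p0 = 1.5%: 7,428 per group (stated: about 7,500).
- p0 = 9%: 1,384 per group (stated: 1,400).

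Both are reproduced when the mid-range allele frequency is entered directly as exposure. Entering dominant carriers, 1 − (1 − q)², gives 3,685 and 795 without the correction, far from the stated figures.

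**Step 2: rare-variant power at the actual numbers.** Var(log OR) = 1/(n1·p1) + 1/(n1·(1 − p1)) + 1/(n0·p0) + 1/(n0·(1 − p0)); power = Φ(ln 1.5 / SE − 1.96).

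Example, SCC at p0 = 1.5%: p1 = 0.0223, SE = 0.233, 0.4055 / 0.233 − 1.96 = −0.22, power 41%.

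| Allele frequency | BCC, frequency as exposure | BCC, dominant carriers | SCC, frequency as exposure | SCC, dominant carriers |
|---|---|---|---|---|
| 1% | 56% | 84% | 30% | 51% |
| 1.5% | 73% | 95% | 41% | 68% |
| 2% | 84% | 98% | 52% | 79% |

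**Step 3: cross-check against the stated 7,500.** Equal-group equivalent n = 2·n1·n0 / (n1 + n0):
- BCC: 2 × 2,363 × 12,267 / 14,630 = 3,963.
- SCC: 2 × 940 × 12,267 / 13,207 = 1,746.

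Scaling so that 7,500 gives 90%, power = Φ(3.2415·√(n / 7,500) − 1.96) = 65% for BCC and 35% for SCC. With all 14,875 controls it is 67% and 35%. With unlimited controls (n = 2·n1) it is 73% and 37%, so case numbers set the limit.

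**Step 4: the article's interaction requirements.** The same scaling, with the stated requirement in place of 7,500:

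| Interaction | Required per group | BCC (3,963) | SCC (1,746) |
|---|---|---|---|
| Rare variant, 2.0 | 5,000 | 82% | 48% |
| Common variant, 1.5 | 3,500 | 93% | 63% |

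Both equivalents exceed the 1,200 needed for common variants at 2.0.

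**Step 5: common-variant main effects.** Both equivalents exceed 1,400. SCC has about 95% power (92% without the 152 cases with both tumours), and BCC more.

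**Step 6: sensitivity to the OR.** With frequency as exposure over 1–2% and 12,267 controls, 90% power is reached at an OR of about 1.55–1.8 for BCC and 1.8–2.2 for SCC.

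**The case against.** The strongest objection is that the 7,500 is a melanoma requirement built on a melanoma OR. The article gives no OR or main-effect requirement for BCC or SCC, so saying that these outcomes fail the article's own main-effect requirement would be too strong. This stands: OR 1.5 is an assumption here, and Step 6 shows what larger effects would do. The document does not allow a judgement on whether such effects are plausible.

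A second objection concerns exposure. A reader might infer from the 7,500 that BCC is plainly underpowered for rare variants. The documents do not support that. The model in the section on combining data is introduced as dominant, with presence of the variant as the exposure, and the section on use of MC1R data leaves the inheritance model to be chosen by fit. Under dominant carriers BCC passes 90% at 1.5% and 2% and misses only at 1%. SCC stays below 90% on this basis too.

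Third, the adequacy sentence is not unqualified, since its ending limits the interaction claim by variant frequency. That narrows the point but leaves the gap by cancer type.

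Fourth, a reader might infer that null results for BCC or SCC will be reported as no association. Nothing in the article says so, and the two-stage estimator comes with a variance, so imprecision will be visible. Data collection had also closed, so the sentence drives no recruitment decision. Both remarks reduce the weight of the point. A condensed article may leave a power table to a fuller document, but here it makes a positive claim that its own counts do not bear out for all outcomes.

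**Conclusion.** The concern holds as an over-broad adequacy statement. No sum in the paragraph is wrong.

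- **SCC, rare variants:** short of 90% at OR 1.5 on every reading, at about 30–52% or 51–79% depending on the exposure definition.
- **SCC, interactions:** short of the article's own requirements for rare variants at 2.0 (about 48%) and common variants at 1.5 (about 63%).
- **BCC, rare variants:** short (56–84%) on the basis that reproduces the 7,500, and largely adequate (84–98%) for dominant carriers. This part is conditional.
- **BCC, interactions:** a modest shortfall for rare variants at 2.0 (about 82%), and adequate for common variants at 1.5 (about 93%).
- **Common-variant main effects:** adequate for both.

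The main-effect figures rest on the carried-over OR and all figures on two-sided 5%. In other respects they are favourable. The two-stage analysis estimates ORs within each study, so controls from studies without NMSC cases add nothing to the BCC and SCC estimates, and between-study variance lowers power further. Whether every melanoma case contributes to the melanoma estimate is a separate question, not examined here.

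**What to change.** Limit the adequacy sentence to main effects for melanoma and to common-variant main effects for BCC and SCC, and say which cancer type the interaction statement applies to. For rare variants and for interactions in BCC and SCC, state either the power or the minimum detectable OR at 90% power. Use the case and control numbers that will enter those analyses, and give the assumed OR, alpha and exposure definition (allele frequency or carriers).

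The cost is a few sentences and one small table. No new data are needed, and the only loss is a less favourable statement of adequacy.

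### The statement that the sample is sufficient rests on a 7,500-case minimum for rare variants, but only 5,160 melanoma cases come from studies that can supply a study-specific odds ratio

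*Protocol article*

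**What the plan says.** The section on the collected data and statistical power gives, for *MC1R* variants and melanoma at an odds ratio of 1.5, the "minimum required sample size to find a statistically significant association". For a variant of low frequency the article puts it at "around 7,500 cases and 7,500 controls for rare variants (1-2% allele frequency in controls"). Its figure for common variants, defined by an allele frequency of 8-10%, is 1,400 per group. Each figure is for 90% power. No significance level is given. Interaction sizes per group follow: 5,000 and 16,000 for rare variants, and 1,200 and 3,500 for common variants (effects 2.0 and 1.5). The paragraph then concludes: "Our sample size therefore is appropriate for the purpose of the analysis, and large enough to allow stratified and interaction analyses". The sentence goes on to single out small interactions for frequent variants and larger ones for less common variants.

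The final dataset is described as 7,806 melanoma cases, 3,151 non-melanoma cases and 14,875 controls. The abstract and the section on combining data into a single dataset both prefer the two-stage method for this project. Its first stage reads: "First, study-specific ORs will be calculated by applying logistic regression to the data from each study".

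**The concern.** A logistic regression within a study that holds only cases, or only controls, gives no odds ratio for cancer. Table 3 shows that such studies are a large part of the collection. The full 7,806 melanoma cases pass the stated 7,500; the cases the preferred method can use do not. The power paragraph makes no deduction for this.

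The conclusion is also worded for the purpose of the analysis as a whole. Aim 1 includes basal cell carcinoma (BCC) and squamous cell carcinoma (SCC), yet only melanoma was sized. At stake is how null results are read: a rare-variant null, above all for SCC, could be taken as adequately powered on the strength of this sentence.

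**Working it through.** **Inputs.** From the power paragraph: OR 1.5, 90% power, minima of 7,500 and 1,400 per group. From Table 3 (study design): case-control, 21 studies, 5,092 melanoma cases, 6,852 controls; case-only, 11 studies, 2,646 melanoma cases; control-only, 6 studies, 1,464 controls; cohort, 1 study, 68 melanoma cases, 6,559 controls. Assumed because not stated: alpha 5%, two-sided.

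**1. Reproducing the stated minima.** For exposure prevalence p0 in controls, p1 = 1.5·p0/(1 − p0 + 1.5·p0), and n = [1.960·√(2p̄(1−p̄)) + 1.2816·√(p0(1−p0) + p1(1−p1))]² / (p1 − p0)².

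- p0 = 1.5%: p1 = 2.233%, n = 7,158, or 7,428 with continuity correction.
- p0 = 9%: p1 = 12.92%, n = 1,334, or 1,384 with continuity correction.
- Without the correction, 7,500 corresponds to p0 of about 1.43%, and 1,400 to about 8.5%.

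The stated minima are therefore reproduced when about 1.4-1.5% and 8.5-9% are entered directly as exposure prevalence.

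**2. Usable melanoma data.**

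- Cases: 7,806 − 2,646 = 5,160 = 5,092 + 68. The source-of-controls rows of Table 3 agree: 509 + 4,651 = 5,160.
- Controls: 14,875 − 1,464 = 13,411 = 6,852 + 6,559.

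**3. Equal-group equivalent.** A study with m cases and n controls carries about the information of 2mn/(m + n) per group.

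- Case-control studies together: 2 × 5,092 × 6,852 / 11,944 = 5,842.
- Cohort: 2 × 68 × 6,559 / 6,627 = 135.
- Total: 5,977 per group.

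This is an upper bound. It treats all 21 case-control studies as having the same case-to-control ratio; any variation in that ratio lowers the sum. The cohort's 6,559 controls add little because they face only 68 melanoma cases.

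**4. Power on the plan's own scale.**

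- Scaling from 7,500: Φ(√(5,977/7,500) × 3.2415 − 1.960) = Φ(0.934) = 82%.
- Direct calculation at p0 = 1.5%, n = 5,977: 84%.

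Both are before any between-study variance, which the random-effects model would add.

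**5. The same data under dominant coding.** Carrier frequency is 1 − (1 − q)² for allele frequency q.

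| Allele frequency | Carriers | n per group needed (5%, 90%) | Melanoma power at 5,977 |
|---|---|---|---|
| 1% | 1.99% | 5,434 | 92.5% |
| 2% | 3.96% | 2,811 | 99.7% |
| 8% | 15.4% | 863 | over 99% |
| 10% | 19.0% | 741 | over 99% |

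**6. SCC.** Cases: 788 + 152 with both types = 940. Taken against all 13,411 controls, the equivalent is at most 2 × 940 × 13,411 / 14,351 = 1,757. If OR 1.5 and dominant carriers are assumed, power is at most 45% at 1% allele frequency and 73% at 2%. This bound is looser than the melanoma one, because Table 3 does not split BCC from SCC by study design.

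**The case against.** The strongest reply is that the shortfall is measured against 7,500, and 7,500 may itself be larger than needed. Under dominant carrier coding at 5%, the need is about 2,800-5,400 and the usable melanoma data are enough. That stands: the comparison faults the printed justification, not the capacity of the data.

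A reader might infer that the main-effect sizes mistakenly use allele frequency as carrier prevalence while the interaction sizes use carriers. The documents do not establish this. With dominant carriers and alpha 0.05/9 (nine variants), allele frequencies of 1.1-1.2% give 7,755-7,133, and 8% gives 1,351 (1,384 with continuity correction), all close to the stated minima. The interaction inputs (exposure prevalence, main effects, alpha) are not given, and more than one set of assumptions comes within about 4% of the four interaction figures, including a one-sided one that uses 2% and 10% as prevalence. An inconsistent basis is a question for the authors.

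It is also fair that the article never names 7,806 as its comparator. Of the six stated sizes, 5,160 cases exceed the common-variant main effect (1,400), both common-variant interactions (1,200 and 3,500) and, narrowly, the larger rare-variant interaction (5,000). The 16,000 was out of reach even with every case, and the sentence's qualifier concedes as much. Case-only studies can still inform variant-phenotype associations under aim 2.

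Crude pooling of 5,160 cases with 13,411 controls would give 2 × 5,160 × 13,411 / 18,571 = 7,453 equivalents, close to 7,500. That ignores the within-study comparison the two-stage model imposes, so it does not answer the point.

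Finally, an article may leave power for BCC and SCC to a fuller document. What remains is that the sentence claims sufficiency for the whole purpose of the analysis after sizing melanoma alone.

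**Conclusion.** The point holds, at moderate severity. The sufficiency conclusion does not follow from the stated minimum once the preferred analysis is applied: 5,160 usable melanoma cases against 7,500, at most about 5,977 per group in equal-group terms, and at most 82-84% power on the plan's own scale where 90% is stated. The case counts come straight from Table 3 and the two-stage model. The power figures rest on a two-sided 5% level, a common case-to-control ratio across the case-control studies, and no between-study variance.

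The shortfall is confined to the rare-variant main effect. It would be wrong to conclude that the melanoma analysis is underpowered: with carrier coding at 5%, the same data give about 92% to over 99% before heterogeneity. For SCC, rare-variant power of at most about 45-73% is conditional on OR 1.5 and carrier coding, neither of which the article states for SCC.

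**What to change.** Rewrite the sufficiency sentence from the studies that hold both cases and controls: 5,160 melanoma cases, not 7,806, with the within-study balance taken into account. Declare the alpha and its sidedness, the inheritance model, and whether frequencies are entered as allele or carrier frequencies. Use these consistently for the main-effect and interaction sizes, and include an allowance for between-study variance. The article plans to compare inheritance models, so the coding is the authors' choice; it needs only to be stated.

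Either limit the claim to melanoma or give power for BCC and SCC separately. Add that a null rare-variant result from an analysis below 90% power is inconclusive.

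The cost is a recalculation and a stated figure that may be less favourable. No new data and no change to the analysis method are needed.

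### Gene-environment interaction power is judged on the whole dataset; among subjects with the exposure recorded, 90% power is missed for rare-variant 2.0 on every exposure and for common-variant 1.5 on all but sunburns

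*Protocol article*

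**What the plan says.** The section on the collected data and statistical power sets four requirements for a two-way gene-environment interaction, all at 90% power. For a rare variant, "around 5,000 cases and 5,000 controls would be needed to observe a multiplicative interaction effect of 2.0". Detecting a weaker interaction with such a variant would take "16,000 cases and 16,000 controls to observe a smaller multiplicative effect of 1.5, both with 90% statistical power". For a common variant, interactions of 2.0 and 1.5 need "around 1,200 cases and 1,200 controls, and with around 3,500 cases and 3,500 controls, respectively".

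The same paragraph defines rare and common through the main-effect sizes, which assume "Odds Ratio (OR) = 1.5". The entry for the rare class reads "7,500 cases and 7,500 controls for rare variants (1-2% allele frequency in controls". Its counterpart for the common class reads "1,400 cases and 1,400 controls for common variants (8-10% allele frequency in controls".

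The paragraph then concludes that the sample is "large enough to allow stratified and interaction analyses, especially to find even small interaction effects with the most frequent variants". For rarer variants it claims only bigger interactions. Against the four requirements, this most naturally means common variants at 1.5 and rare variants at 2.0. The paragraph gives no count by exposure. The only sample it can refer to is the final dataset described at the start of the section.

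Table 1 gives the number of subjects with each variable recorded. The section on combining data into a single dataset says that most missing data arise because some studies did not collect a variable. It expects bias from both imputation and missing-data indicators in that situation, and prefers a two-stage analysis.

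**The concern.** A subject whose study did not record an exposure says nothing about the interaction between that exposure and a variant, and the plan does not intend to fill the gap by imputation. The relevant sample is therefore the Table 1 count for that exposure, not the total. Environmental exposures are recorded in only 7% to 20% of controls.

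The plan ends its joint-association section with gene-environment analyses, and this sentence is its only statement on whether the data can support them. If it overstates power, readers will give a null interaction more weight than it can bear. The article also offers itself as methodological guidance, so the practice of judging interaction power on the total sample may be copied.

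**Working it through.** **Reproducing the plan's sizes.** A two-proportion calculation (two-sided 5%, 90% power, OR 1.5, allele frequency used as prevalence in controls) gives about 7,400 per group at 1.45% and about 1,400 at 8.5%. The stated figures are 7,500 and 1,400.

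For the interaction sizes, the article gives neither exposure prevalence nor main effects. Assuming exposure prevalence 0.3, both main-effect ORs 1.5, and carrier prevalence 3% (rare) or 17% (common), a Wald test on the log interaction OR needs 5,142, 15,608, 1,166 and 3,476 per group. The stated figures are 5,000, 16,000, 1,200 and 3,500, so all four agree within 3%. The stated sizes are taken as correct below, so the main comparison does not depend on these assumptions.

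**Method.** For *a* cases and *b* controls with the exposure recorded (Table 1), the equal-group equivalent is n = 2ab/(a+b). Power is Φ(3.2415 × √(n/N) − 1.96), where N is the plan's required size and 3.2415 = 1.96 + 1.2816. A two-sided 5% level is assumed, since the article states none.

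Example, artificial UV in melanoma, rare variant 2.0: n = 2 × 3,842 × 1,058 / 4,900 = 1,659. Then 3.2415 × √(1,659/5,000) − 1.96 = −0.093, and power is 46.3%.

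**Full dataset.** n = 2 × 7,806 × 14,875 / 22,681 = 10,239. Power is 99.6% for rare 2.0 and almost 100% for common 1.5, so the sentence holds on this denominator.

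**Melanoma, subjects with the exposure recorded**

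| Exposure | Cases / controls | n | Rare 2.0 | Common 1.5 | Common 2.0 |
|---|---|---|---|---|---|
| Sunburns | 4,210 / 2,968 | 3,482 | 77.2% | 89.8% | >99% |
| Intermittent sun | 4,493 / 2,286 | 3,030 | 71.3% | 85.5% | >99% |
| Continuous sun | 4,909 / 1,938 | 2,779 | 67.6% | 82.3% | >99% |
| Smoking | 2,266 / 2,286 | 2,276 | 59.0% | 74.3% | 99.4% |
| Artificial UV | 3,842 / 1,058 | 1,659 | 46.3% | 60.7% | 96.8% |

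**Pooled NMSC, same controls**

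| Exposure | Cases | n | Rare 2.0 | Common 1.5 | Common 2.0 |
|---|---|---|---|---|---|
| Sunburns | 1,288 | 1,796 | 49.3% | 64.1% | 97.8% |
| Intermittent sun | 1,266 | 1,630 | 45.6% | 59.9% | 96.5% |
| Continuous sun | 741 | 1,072 | 32.3% | 43.4% | 86.5% |
| Smoking | 419 | 708 | 23.0% | 30.8% | 70.2% |
| Artificial UV | 298 | 465 | 16.6% | 21.8% | 52.3% |

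**Case-only studies.** Table 3 places 2,646 of 7,806 melanoma cases (34%) in case-only studies, which cannot yield a study-specific case-control estimate. Table 1 is not split by design. If these cases drop out in proportion for every exposure (assumption), melanoma power in the order of the table becomes 69.0, 64.4, 61.7, 49.6 and 42.5% for rare 2.0, and 83.6, 79.5, 77.0, 64.5 and 56.3% for common 1.5. Common 2.0 stays at 95% or more.

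**Sensitivity.** The equal-group conversion treats case and control variances alike. Separate variances, with exposure prevalence 0.2 to 0.5 and both main-effect ORs 1 or 1.5, give 88–92% for sunburns and 53–60% for artificial UV (common 1.5), and 74–80% and 38–44% (rare 2.0). The pattern does not change.

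**Phenotype.** Table 1 has hair color in 6,841 melanoma cases and 11,889 controls, and eye color in 5,990 and 10,720. Both exceed 5,000/5,000.

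**The case against.** The strongest reply has four parts.

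- **Breadth of the sentence.** It covers stratified and interaction analyses in general. The interaction named in the project's third aim is between *MC1R* and phenotype, for which hair and eye color counts are ample. Gene-environment work is not a numbered aim. This stands, and it limits the point to environmental exposures. It does not remove it, because the sizes from which the sentence draws its conclusion are gene-environment sizes.
- **Counting controls alone.** No exposure has 3,500 controls, so a reader might infer that common 1.5 fails throughout. That is too strong. Surplus cases offset scarce controls, and sunburns in melanoma reaches an equivalent of 3,482 against a requirement of around 3,500.
- **What remains well powered.** A reader might infer that 90% power survives only for common 2.0 in melanoma. The figures do not support this: common 2.0 is also met in pooled NMSC for sunburns and intermittent sun.
- **Consequence.** A reader might infer that a null result would be worthless, or that the authors will read it as absence of interaction. Power of 68–90% for sunburns and the two sun-exposure variables in melanoma is not inability to detect, and the article does not say how null interactions will be interpreted.

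Two inputs are also uncertain. The case-only loss is an assumption, and the article leaves its gene-environment methods open, so exclusion of those cases is not established. Smoking and intermittent sun show the same control count (2,286), which should be checked against the database.

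**Conclusion.** The adequacy statement is wrong as written for gene-environment interaction. In melanoma, 90% power is reached for no environmental exposure with a rare variant and interaction 2.0 (46–77%). With a common variant and interaction 1.5 it is reached only approximately, for sunburns; the other four exposures have about 61–85%. If case-only cases drop out proportionately, sunburns also falls, to about 84%.

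In pooled NMSC, power is 17–49% for rare 2.0 and 22–64% for common 1.5. Common 2.0 falls short for continuous sun, smoking and artificial UV (about 87%, 70% and 52%). Separate basal cell and squamous cell analyses would have less.

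These results rest on the plan's stated sizes, a two-sided 5% level and the equal-group conversion. They include no allowance for between-study variance, which would lower power further. The required sizes themselves are not in dispute; the fault is the sample they are compared with.

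**What to change.** Replace the adequacy sentence, as it applies to gene-environment interaction, with a table by exposure and cancer type (melanoma, BCC, SCC). Give power or the minimum detectable interaction for rare and common variants. Compute it from subjects who have both genotype and exposure in studies with cases and controls, and state the significance level, exposure prevalence and main effects assumed.

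Say that 90% power is not reached for rare-variant 2.0 on any environmental exposure, nor for common-variant 1.5 except approximately for sunburns in melanoma, and label those analyses exploratory. Report common-variant 2.0 where it is adequate, including pooled NMSC for sunburns and intermittent sun, rather than confining adequate power to melanoma. Keep the favourable statement for hair and eye color. Verify the repeated control count of 2,286 while building the table.

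The cost is text and one table from data already held, with a less favourable stated power.
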